## Abstract

**Background:**

Cervical radiculopathy caused by spondylotic foraminal stenosis may require surgical treatment. Surgical options include anterior cervical foraminotomy and fusion or posterior cervical foraminotomy. Controversy remains regarding the preferable surgical approach. Pertinent clinical evidence is limited to low-quality observational reports. Therefore, treatment decisions are predominantly based on the individual surgeon’s preference and skill. The study objective is to evaluate the efficacy and safety of posterior foraminotomy in comparison to anterior foraminotomy with fusion for the treatment of spondylotic foraminal stenosis.

**Methods/design:**

This is a multicenter randomized, controlled, parallel group superiority trial. A total of 88 adult patients are allocated in a ratio of 1:1. Sample size and power calculations were performed to detect the minimal clinically important difference of 14 points, with an expected standard deviation of 20 in the primary outcome parameter, Neck Disability Index, with a power of 80%, based on an assumed maximal dropout rate of 20%. Secondary outcome parameters include the Core Outcome Measures Index, which investigates pain, back-specific function, work disability, social disability and patient satisfaction. Changes in physical and mental health are evaluated using the Short Form-12 (SF-12) questionnaire. Moreover, radiological and health economic outcomes are evaluated. Follow-up is performed 3, 6, 12, 24, 36, 48 and 60 months after surgery. Major inclusion criteria are cervical spondylotic foraminal stenosis causing radiculopathy of C5, C6 or C7 and requiring decompression of one or two neuroforaminae. Study data generation (study sites) and data storage, processing and statistical analysis (Department of Medical Statistics, Informatics and Health Economics) are clearly separated. Data will be analyzed according to the intention-to-treat principle.

**Discussion:**

The results of the ForaC study will provide surgical treatment recommendations for spondylotic foraminal stenosis and will contribute to the understanding of its short- and long-term clinical and radiological postoperative course. This will hopefully translate into improvements in surgical treatment and thus, clinical practice for spondylotic foraminal stenosis.

**Trial registration:**

Current Controlled Trials: ISRCTN82578069.

**Electronic supplementary material:**

The online version of this article (doi:10.1186/1745-6215-15-437) contains supplementary material, which is available to authorized users.

## Background

Cervical radiculopathy is a clinical diagnosis defined by the presence of sensory or motor deficits and complaints caused by mechanical compression of the corresponding cervical nerve root. Degenerative etiologies include disc herniation, spinal canal stenosis and spondylotic foraminal stenosis. Cervical radiculopathy remains a potentially disabling disease with a significant impact on the patient’s quality of life. Despite adequate conservative non-operative therapy, a large number of patients will require surgical treatment. Widely used options in this setting include anterior cervical discectomy and fusion, cervical arthroplasty, and posterior cervical foraminotomy. Moreover, a significant increase in the frequency of surgical treatment has been reported within the past decade. From 1999 to 2008, the annual number of cervical discectomies with subsequent fusion for degenerative disc diseases in the USA increased by 67% [1]. In a larger retrospective survey, however, spondylotic foraminal stenosis accounted for only approximately 20% of the surgical interventions in the degenerative cervical spine [2]. Of these, around two-thirds were due to unilateral foraminal stenosis, whereas one-third comprised decompression of two or more stenotic foramina, emphasizing the multifocal nature of the disease. Although posterior approaches to the cervical spine had been described almost a decade earlier than the anterior approaches [3, 4], anterior discectomy has become the gold standard for treating cervical degenerative disc diseases resulting in encroachment of the central spinal canal [5–7]. For lateral pathologies, however, there is still controversy regarding the most adequate surgical approach. Most pertinent literature in this matter consists of low-quality observational reports. Analyses of three comparative studies on the treatment of cervical disc herniation yield inconclusive results. One group of investigators observed an advantage in the anterior approach in terms of short-term neurological recovery [8]. In turn, other authors have reported significant benefits of the posterior approach regarding the average time to return to unrestricted full duty of military personnel [9]. A low-quality randomized controlled trial comparing the two surgical approaches in the treatment of acute cervical disc herniations did not show any significant difference in outcome [10]. To the best of our knowledge, prospective comparative data primarily investigating spondylotic foraminal stenosis is still lacking. Even non-comparative retrospective data on spondylotic foraminal stenosis is scarce. Studies on posterior foraminotomy reported good outcomes in 64% to 96% of patients and re-operation rates of around 4% to 7% [11–13]. The few studies exclusively investigating anterior cervical foraminotomy and fusion reported 83% to 91% good results and re-operation rates of 4% to 14% [14, 15]. Possible advantages of anterior cervical foraminotomy are direct access to remove anterior osteophytes and the option of decompressing the foramina bilaterally using a single surgical access. Moreover, the insertion of a cage provides an additional indirect decompressive effect of the foramina. This approach also offers the important option of sagittal correction in cases with segmental kyphosis. A potential disadvantage of anterior fusion might be the precipitation of adjacent segment disease. In reviewing 409 anterior cervical fusions, Hilibrand and colleagues [16] reported a relatively constant rate of symptomatic adjacent segment disease of 2.9% per year, with 25.6% of patients developing adjacent segment disease within 10 years of the operation and 7.5% of these patients requiring a re-operation. By contrast, single-level posterior foraminotomy for cervical radiculopathy displayed an annual 0.7% rate of adjacent segment disease cumulating to 6.7% at 10 years and a re-operation rate of 3.2% [17]. A potential advantage of posterior cervical foraminotomy is the maintenance of segmental motion in the majority of treated segments, reducing the likelihood of adjacent segment degeneration, as outlined. Two major concerns with posterior foraminotomies are: (1) persistent neck and shoulder pain secondary to muscle stripping performed during the conventional open approach and (2) same-level degeneration and kyphosis secondary to partial resection of the facet joint. The latter issue is the subject of some controversy. A frequently cited *in-vitro* study has shown that non-physiological segmental mobility of the cervical spine occurs when posterior foraminotomy involves resection of more than 50% of a facet joint [18]. However, other studies demonstrated that, even in cases of extensive facetectomy, a cervical motion segment will remain stable if all the anterior elements and one additional posterior element, such as the interspinous and supraspinous ligaments, are left intact [19, 20]. A clinical study, supporting these biomechanical results, reported favourable outcomes in more than 90% of the patients five years after posterior cervical foraminotomy including routine removal of 75% of the facet joint [21].

The study objective is to evaluate the efficacy and safety of posterior foraminotomy compared with anterior foraminotomy with fusion for the treatment of spondylotic foraminal stenosis. Both surgical approaches are well-established techniques in clinical practice and can be performed with comparable low risk. The surgical risk profiles of the approaches differ according to local anatomical features. Anterior surgery includes risks of injury of cervical viscera, nerves (laryngeal recurrent nerve, sympathetic chain) and vessels. Moreover, placement of an intervertebral fusion cage might potentially result in implant dislocation, pseudarthrosis and adjacent segment disease. Specific risks of the posterior approach are advancing degeneration of the affected level and progressive kyphotic deformity. Participation in the study does not result in specific benefits for the patient.

## Methods/design

### Study design

The ForaC study is a multicenter randomized, controlled, parallel group superiority trial with 88 adult patients allocated to the groups in a 1:1 ratio. The expected enrolment time is 2 years, and the conclusion of the study is estimated at 7 years. The primary study endpoint is the difference in Neck Disability Index between treatment groups at five years after intervention. As one of the secondary study endpoints, the Core Outcome Measures Index is applied to assess pain, back-specific function, work disability, social disability and patient satisfaction. Moreover, changes in physical and mental health are assessed by the Short Form-12 (SF-12) questionnaire, version 2. Adjacent level degeneration, segmental lordosis and overall cervical sagittal alignment are determined by flexion or extension X-rays and magnetic resonance imaging. Pre-operative American Society of Anesthesiologists grade staging might allow the identification of risk factors. Neurological status and the quality and quantity of current pain medication are documented. Operation time and time of hospitalization are documented. Quantitative sensory testing is performed to assess and quantify sensory nerve function non-invasively. We also evaluate the direct costs of hospital care and the indirect costs of follow-up treatment outside the hospital. Costs of surgery and hospitalization, including duration of inpatient treatment, cost of nursing, costs of medication and physiotherapy, are assessed after discharge from the hospital according to internal cost-estimate lists from the hospital operator. In addition, the indirect costs following discharge from hospital (for example, including physiotherapy, rehabilitation centres, pain medication, medical consulting) are documented on a routing sheet. Each study participant will receive such a routing sheet when leaving the hospital, with instructions for documentation. Postoperative care is not standardized in the study protocol and is to be performed according to the standard of care for spondylotic foraminal stenosis surgery at the participating sites. An external orthosis is not used in either group. Primary and secondary outcome parameters are outlined in more detail in Table 1. Ethics approval was attained at the local research ethics committee of the Medical University Innsbruck (UN4702). This study complies with the World Medical Association Declaration of Helsinki Ethical Principles for Medical Research Involving Human Subjects, 2008.

**Table 1 Tab1:** **Primary and secondary outcome parameters**

Primary outcome parameter	Neck Disability Index at five years’ follow-up
Secondary outcome parameters	Core Outcome Measures Index
	Individual patient success at 12, 24, 36, 48 and 60 month defined as:
	● Improvement of at least 17 in the Neck Disability Index (100 points) compared with baseline (adjustable according to results from own minimal clinically important change results for Neck Disability Index).
	● Pain relief, as defined by ≥20 mm improvement on 100 mm visual analog for arm/shoulder pain
	● Global outcome (1 or 2 on five-category Likert scale)
	● No opiates or opiate derivatives because of neck or arm pain
	● Absence of symptomatic device failure and re-operations at the index level
	Pain relief, as defined by ≥20 mm improvement on 100 mm visual analog scale for neck pain and arm or shoulder pain
	Changes in physical and mental health defined as improvement of 15% in the overall score as captured by the Short Form-12 (SF-12) version 2 questionnaire (Brazier 2005)
	Modified Japanese Orthopedic Association score and Nurick score
	Adjacent level degeneration:
	● By evidence of instability, defined as sagittal plane translation >3.5 mm (20% of vertebral body anterior-posterior diameter) or sagittal plane rotation of >20° based on standing flexion or extension X-rays
	● By evidence of disc degeneration (Miyazaki grade ≥ IV) or osteochondrosis (Modic change type I) on magnetic resonance imaging
	● Radiographic classification (Walraevens 0 to 3)
	● By occurrence of operation because of adjacent level disease
	Quantitative sensory testing
	Segmental lordosis and overall cervical sagittal alignment
	Operative time
	Length of hospital stay
	Pain medication usage (including epidural injections and nerve block injections)
	Return to work
	Worker’s compensation
	Direct and indirect societal costs

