#### Sample size and power calculation

The sample size calculation is based on the primary endpoint of the study, the group difference in the Neck Disability Index. A reduction in Neck Disability Index score of 14 to 17 points out of 100 is considered to be clinically meaningful [22, 23]. Thus, 14 points were used as the required difference between groups applicable for the power calculations. Moreover, a group standard deviation of 20 is assumed, based on results of comparable previous trials [24, 25]. A sample size calculation was performed based on a two-group *t* test (GraphPad StatMate Software, version 2.0); 35 patients per group are required to detect a 14-point difference with 80% power on a two-sided level of significance of 0.05. A loss to follow-up of less than 20% was considered adequate for final calculation of sample size. Accordingly, the proposed sample size amounts to 88 patients, that is, 44 patients in each group. In case of non-normality of the Neck Disability Index, this sample size is also sufficient to detect a difference of 14 points with a Mann-Whitney *U* test.

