#### Statistical analysis

Endpoints will be analyzed as appropriate depending on data distribution with a two-sided 0.05 level of significance. Detailed descriptive statistics will be provided for the data collected and 95% confidence intervals will be calculated for all relevant estimates. Clinical follow-up data will be analyzed by analysis of covariance (ANCOVA) or generalized model alternatives for categorical or semiquantitative data. Changes within the treatment groups over time as well differences between groups will be assessed simultaneously. The primary analysis will follow the intention-to-treat principle. All randomized patients with a complete preliminary examination will be considered for inclusion into the intention-to-treat population. Further sensitivity analysis will be provided to evaluate robustness of the results with regard to unexpected circumstances (for example, impact of ‘cross-over’ patients who are not treated as randomized but are required to be analyzed as randomized (intention-to-treat principle) and centre effects. Secondary endpoints will be analyzed in an exploratory manner at a two-sided significance level of 5%. Safety and tolerability parameters will be analyzed descriptively. Frequencies will be compared by Chi-square or Fisher’s exact tests, as appropriate. Analysis of time-dependent probabilities of critical events will be performed using the Kaplan-Meier method. Furthermore, multivariate event analyses will be performed using Cox proportional hazard regression models. The last-observation-carried-forward approach will be employed, in order to perform an intention-to-treat analysis of the primary efficacy endpoint in consideration of all randomized patients. In addition, for the purpose of a supportive sensitivity analysis, multiple imputation procedures will be applied. Statistical analysis will be performed 12, 24, 36 and 60 months after completion of the last visit of the study population at the specified time points.

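### The SF-12 outcome is fixed as a yes/no 15% improvement in one overall score, so it cannot show physical and mental health separately and loses power that a continuous analysis of the same data would keep

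*Protocol article*

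**What the plan says.** All references are to the protocol article.

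- **Purpose.** The abstract (Methods/design) says "Changes in physical and mental health are evaluated using the Short Form-12 (SF-12) questionnaire". The Study design section repeats that "changes in physical and mental health are assessed by the Short Form-12 (SF-12) questionnaire, version 2".
- **Outcome definition.** Table 1 fixes the outcome as "Changes in physical and mental health defined as improvement of 15% in the overall score" of the questionnaire, with an in-text citation. It names one score, one threshold and one direction. It does not say what the 15% is a percentage of.
- **Analysis.** The Statistical analysis section says "Clinical follow-up data will be analyzed by analysis of covariance (ANCOVA) or generalized model alternatives for categorical or semiquantitative data". Secondary endpoints are exploratory, tested two-sided at 5%.
- **Data.** The visit plan (Table 3) collects the SF-12 before surgery, three days after it and at every follow-up from 3 to 60 months.
- **Power.** No effect size, SD or power is given for the SF-12. The sample size rests on the Neck Disability Index alone.

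**The concern.** The definition does not match the purpose. The outcome is named for two dimensions of health, but the rule records whether one total rose by 15%. A physical gain offset by a mental loss, or the reverse, appears as no improvement. Deterioration is also a change, yet a patient who worsens and one who gains 14% fall into the same category.

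The threshold also decides which analysis applies. The Statistical analysis section uses ANCOVA for follow-up data and sends categorical data to generalized models. A responder outcome falls under the second route, so the definition moves the SF-12 away from the more efficient method the plan already contains.

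The SF-12 is the only general-health questionnaire the article describes. What is at stake is whether the trial can say anything clear about physical and mental health after the two operations, with about 35 evaluable patients per group at the planned dropout.

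**Working it through.** **1. The plan's own figure.** Inputs from the Sample size section: difference 14, SD 20, two-sided 5%, 80% power, 20% loss.

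- Standardised effect: d = 14/20 = 0.70.
- The normal approximation gives 33 per group. The exact t test needs 34 (power 0.812) and gives 0.823 at 35. The stated 35 reproduces to within two patients.
- Dropout: 35/(1 − 0.20) = 43.75, so 44 per group and 88 in total. This agrees with the plan.

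**2. Cost of the threshold at the trial's own design effect, without baseline adjustment.** The article gives no SF-12 effect, so I assume d = 0.70 for the SF-12 as well. A normal score is cut so that a share p1 of the lower arm responds. The other arm then responds with p2 = 1 − Φ(c − d), where c = Φ⁻¹(1 − p1).

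Example with p1 = 0.50: c = 0 and p2 = Φ(0.70) = 0.758.

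- Difference: 0.758 − 0.500 = 0.258.
- SE under the null, pooled p = 0.629: √(2 × 0.629 × 0.371/35) = 0.1155.
- SE under the alternative: √((0.500 × 0.500 + 0.758 × 0.242)/35) = 0.1113.
- Power: Φ((0.258 − 1.96 × 0.1155)/0.1113) = Φ(0.285) = 0.61.

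| Responders in lower arm | Power of yes/no outcome, 35 per group | n per group for 80% power |
|---|---|---|
| 20% | 59% | 57 |
| 30% | 63% | 52 |
| 40% | 63% | 52 |
| 50% | 61% | 54 |
| 60% | 57% | 60 |
| 70% | 50% | 71 |
| 80% | 40% | 92 |

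The uncut score has 82% power at 35 per group and needs 33 per group for 80%. The yes/no version therefore needs 52/33 = 1.6 to 92/33 = 2.8 times as many patients. With all 44 per group the contrast is 90% against 49% to 73%. At d = 0.50 and 35 per group it is 54% against 26% to 38%.

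**3. Cost under an SF-12-like example.** All inputs are assumed: baseline mean 38 (SD 9), follow-up mean 45 (SD 10), correlation 0.5, 35 per arm. Response means a follow-up score at least 1.15 times the patient's own baseline. Simulated power:

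| True difference | ANCOVA | Baseline-adjusted logistic | Chi-square |
|---|---|---|---|
| 6 points | about 80% | about 55% | about 48% |
| 8 points | about 97% | about 78% | about 70% |

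At 6 points the full gap is 80 − 48 = 32 percentage points. Of this, 55 − 48 = 7 (about a fifth) comes from comparing an adjusted test with an unadjusted one. The other 80 − 55 = 25 points come from the threshold.

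**4. Baseline dependence, if 15% is relative to own baseline.** The hurdle is 0.15 × baseline: 4.5 points at 30, 6.0 at 40, 9.0 at 60 (illustrative baselines; the article gives none). In the example with no treatment difference, responder rates by baseline third are 78%, 56% and 31%. The chi-square test still rejects in about 4% of null trials and the adjusted logistic model in just under 5%, so the comparison between arms stays valid.

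**The case against.** The strongest reply is that little hangs on this. The SF-12 is one of many secondary outcomes, all exploratory, and the plan claims no power for it. The Statistical analysis section also promises detailed descriptive statistics and 95% confidence intervals and does not forbid a continuous analysis. The questionnaire is collected at every follow-up, and an article condenses a fuller protocol. All of that stands and limits the weight of the point. It does not remove it: Table 1 states a rule, and the rule does not match the purpose stated twice elsewhere.

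Second, any responder rule treats worsening like a near miss, including the 20 mm pain rule in the same table. That is true. Here, though, the outcome is named as change in two dimensions, and no continuous SF-12 analysis is named beside it.

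Third, setting ANCOVA against an unadjusted chi-square test overstates the loss, because the planned generalized models can adjust for baseline. This is correct and is why the adjusted responder model is shown; most of the gap remains.

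Stronger readings are tempting but unsupported:

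- **That the result depends on baseline more than on the operation.** The gradient by baseline third was computed with no treatment effect, so it cannot compare the two influences. Randomisation balances baseline on average, and the type I error holds.
- **That patients starting above 1/1.15 = 87% of the maximum can never succeed.** This needs a bounded scale starting at zero and patients near its top. Entry requires a Neck Disability Index of at least 30 and arm or shoulder pain of at least 30 mm, and nothing suggests such patients would be enrolled.
- **That the hurdle certainly varies by patient.** If 15% means 15% of the scale, it is uniform. How the overall score is built rests on a citation that cannot be checked here.

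**Conclusion.** The point holds as a modest, cheaply corrected fault in one secondary outcome. Two parts follow from Table 1 on any reading of the 15%: one thresholded score cannot report physical and mental health separately, and it does not distinguish deterioration from a gain just under the threshold. A third part, the hurdle that varies with baseline, is conditional on 15% being relative to the patient's own baseline; it costs precision and interpretability and introduces no bias.

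The loss of power is substantial in both calculations, but its size rests on assumptions, because the article gives no SF-12 mean, SD, effect or responder rate. A reader might infer that the trial as a whole is underpowered or its main result compromised. The documents do not support that: the Neck Disability Index endpoint and its sample size are untouched.

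**What to change.** In Table 1, define the SF-12 outcome as the physical score and the mental score separately, each analysed as a continuous value by ANCOVA with its own baseline as covariate. If an overall score is kept, analyse it the same way. Keep the 15% improvement rate as a supplementary descriptive figure, and state whether 15% refers to the patient's own baseline or to the scale.

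The cost is one line in Table 1 or the analysis plan. The questionnaire, the visits and the method are already planned, and no further patients or data are needed. The downside is two scores to report in place of one, with slightly more multiplicity among outcomes that are already exploratory.

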**Table 2 Tab2:** **Inclusion and exclusion criteria**

Inclusion criteria	Age between 18 and 80 years
	Cervical spondylotic foraminal stenosis causing radiculopathy of C5, C6, or C7 and requiring decompression of ≤2 neuroforaminae
	Radiculopathy is defined as pain, paralysis or paresthesia in corresponding nerve root distribution areas of C5, C6, or C7, and must include at least arm or shoulder pain with minimum of 30 mm on a 100 mm visual analog scale
	Neck Disability Index score ≥30 out of 100
	Unresponsive to non-operative treatment for six weeks or presence of progressive symptoms or signs of nerve root compression in the face of conservative treatment
	Spondylotic foraminal stenosis (determined by magnetic resonance imaging and computed tomography) at treatment level correlating to primary symptoms
	Appropriate candidate for treatment using either of:
	● Anterior approach via ventral discectomy and fusion
	● Posterior approach via foraminotomy, as described by Frykholm
	Psychosocially, mentally, and physically able to fully comply with this protocol, including adhering to scheduled visits, treatment plan, completing forms, and other study procedures
	Personally signed and dated informed consent document prior to any study-related procedures, indicating that the patient has been informed of all pertinent aspects of the trial
Clinical exclusion criteria	Previous cervical spinal surgery at index level
	Lumbar or thoracic spinal disease to the extent that surgical consideration is probable or anticipated within 6 month after the cervical surgical treatment
	Upper extremity degenerative joint diseases (that is, shoulder) to the extent that:
	● Surgical consideration is likely or anticipated within 6 month after the cervical surgical treatment
	● Resulting pain is chronic (>3 month)
	Axial neck pain in the absence of other symptoms of radiculopathy justifying the need for surgical intervention
	Myelopathy
	Neoplasia as the source of symptoms
	Fixed or permanent neurological deficit unrelated to the cervical disc disease
	Disease or conditions that preclude accurate clinical evaluation (for example, neuromuscular disorders)
	Active or chronic infection, systemic or local
	Systemic disease, including HIV, AIDS, or hepatitis

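### The MRI criterion for adjacent level degeneration is a status without reference to the preoperative scan, so counting it as written mixes pre-existing with new degeneration and weakens the contrast between arms

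*Protocol article*

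**What the plan says.** Table 1 of the protocol article lists adjacent level degeneration as a secondary outcome with four criteria:

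- Instability: "By evidence of instability, defined as sagittal plane translation >3.5 mm", or a rotation limit of 20°.
- MRI: "By evidence of disc degeneration (Miyazaki grade ≥ IV) or osteochondrosis (Modic change type I) on magnetic resonance imaging".
- A radiographic class from 0 to 3, with no cut-off.
- Surgery: "By occurrence of operation because of adjacent level disease".

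The MRI criterion does not mention the preoperative scan. Elsewhere the same table does tie an outcome to baseline: the Neck Disability Index success item reads "Improvement of at least 17 in the Neck Disability Index (100 points) compared with baseline".

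Table 2 admits a wide age range ("Age between 18 and 80 years"). Its only exclusion that names adjacent levels concerns kyphosis. It excludes earlier cervical surgery at the index level only. It also excludes marked instability, set at more than 3 mm of translation or 20° of angulation. Nothing in it refers to Miyazaki grade or Modic change.

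Table 3 schedules MRI before surgery and at 3, 24 and 60 months. The Statistical analysis section treats all secondary endpoints as exploratory at a two-sided 5% level.

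**The concern.** The Background argues about new disease. It cites a fusion series with "25.6% of patients developing adjacent segment disease within 10 years of the operation", contrasts it with a lower rate after posterior foraminotomy, and names preserved segmental motion as the possible reason. That is a question about incidence after surgery. A criterion met by any scan showing the threshold grade answers a different question: how many patients have degenerated adjacent discs at follow-up, whenever this arose.

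A patient who is positive before surgery and stays positive counts in either arm and carries no information about the operation. Such patients dilute the comparison. At stake is a null finding on this outcome that is read as evidence against an advantage of the posterior approach, when the definition itself contributed to it.

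**Working it through.** **The plan's own figure.** The article gives no rate, power or sample size for adjacent level degeneration. Its only calculation is for the Neck Disability Index: difference 14, SD 20, two-sided 5%, 80% power, 35 per group. An exact two-sample t test needs 34 per group, and 35 gives 82% power. Then 35 / 0.8 = 43.75, so 44 per group and 88 in total. The figure holds, and nothing below changes it.

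**Model.** Let q be the share meeting the MRI criterion at baseline (equal in both arms in expectation, by randomisation), and let pA and pP be the risks of new onset after anterior and posterior surgery. If baseline findings persist:

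- follow-up rate in an arm = q + (1 − q)p
- risk difference = (1 − q)(pA − pP)

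**Illustration 1: the Background's 10-year rates, 25.6% and 6.7%.** These are rates of adjacent segment disease, not of MRI grades, and the trial follows patients for 5 years. They only show how the formula behaves. The values of q are assumptions.

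| q | Anterior | Posterior | Difference (points) | Ratio |
|---|---|---|---|---|
| 0 | 25.6% | 6.7% | 18.9 | 3.82 |
| 10% | 33.0% | 16.0% | 17.0 | 2.06 |
| 20% | 40.5% | 25.4% | 15.1 | 1.60 |
| 40% | 55.4% | 44.0% | 11.3 | 1.26 |
| 60% | 70.2% | 62.7% | 7.6 | 1.12 |

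For example, at q = 40%: 0.4 + 0.6 × 0.256 = 0.554 and 0.4 + 0.6 × 0.067 = 0.440.

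**Illustration 2: power.** Exact two-sided Fisher test, 35 evaluable patients per arm, assumed new-onset risks of 40% and 10% (neither is in the article).

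| q | Status at follow-up | New onset, baseline-negative only (n per arm) |
|---|---|---|
| 0 | 78% | 78% (35) |
| 10% | 60% | 75% (32) |
| 20% | 45% | 66% (28) |
| 40% | 23% | 52% (21) |

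If worsening is counted in all patients, and its risk does not depend on the baseline grade, power stays at 78% for every q.

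**Illustration 3: the Background's annual rates, 2.9% and 0.7%, over 5 years.** At a constant rate, 1 − exp(−5 × 0.029) = 13.5% and 1 − exp(−5 × 0.007) = 3.4%. Fisher power with 35 per arm is 14% even at q = 0, and 8% with 21 per arm. For an effect of this size the trial is too small under either definition.

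**Which criteria are affected.** An operation is a new event. The instability limits (3.5 mm, 20°) lie at or above the entry limits (3 mm, 20°), so few patients should be positive at baseline. The radiographic class has no cut-off, so it has no prevalent event, but it too is not tied to a preoperative value. The dilution therefore applies to the MRI criterion.

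**The case against.** The strongest reply is that Table 1 gives grading thresholds, not a counting rule. It sets no time point, does not say whether the unit is the level or the patient, and does not say that a baseline-positive patient is an event. Many other entries in the table are bare measures. The Statistical analysis section says that change over time and group differences are assessed together, and how a graded imaging outcome uses its baseline could be left to a fuller document.

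Part of this stands: the article does not state that prevalent cases will be counted, so the point is conditional on counting the criterion as written. It does not remove the point. The sentence on change over time follows one about clinical follow-up data and does not redefine the imaging event. The criterion is also a definition that the article itself fixes, beside an item in the same table that does name baseline.

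A second reply is that the size is unknown. This stands. No baseline prevalence is given. The Background's remark that the disease is multifocal refers to patients who need two or more foramina decompressed, not to adjacent disc grades. The upper age limit of 80 comes with a lower limit of 18. A reader might infer that many patients are positive before surgery; the article makes this possible but does not show it.

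**Conclusion.** The point holds for the MRI criterion. Read as written it is a status, nothing at entry screens out patients who already meet it, and for any q above zero the risk difference shrinks by (1 − q). This rests on persistence of baseline findings, equal q in both arms, and the same status at follow-up for baseline-positive patients in either arm. Findings that resolve would lessen the loss of power.

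Three stronger readings are not supported:

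- **That adjacent level degeneration as a whole is compromised.** The operation criterion is incident, and the instability criterion is largely cleared at entry.
- **That the comparison is biased towards one approach.** Randomisation balances q on average, so the harm is lost contrast and power plus chance imbalance.
- **That the definition alone would make the trial miss a fusion effect.** With the Background's own annual rates, power is low under any definition. The larger losses shown above depend on assumed risks and an assumed q.

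The outcome is secondary and exploratory. The five-year Neck Disability Index comparison is unaffected. This is a modest defect, worth correcting because the remedy is cheap.

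**What to change.** In Table 1, define the MRI outcome in all randomised patients as worsening against the preoperative MRI at an adjacent level: new Miyazaki grade IV or higher or new Modic type I where absent at baseline, or an increase of at least one Miyazaki grade. Analyse the 0 to 3 radiographic class as change from, or adjusted for, the preoperative class. Report baseline and follow-up status prevalence by arm descriptively.

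A new-onset analysis restricted to baseline-negative patients should be supportive only, because it drops the share q of patients and costs power, as the second table shows.

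Cost: no new visit or scan, since the preoperative and follow-up MRIs are already in Table 3. The preoperative images must be graded. One limitation remains: discs already at the top grade cannot worsen further on that scale, so their number should be reported by arm.
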